### Statistical **analysis**

An MS Excel spreadsheet application will code and record the data. Programming or SPSS v23 will be utilized to analyze the data. For continuous variables, descriptive statistics will be explained as means/standard deviations, IQR/ medians, and percentages/ frequencies; categorical variables will take the form of a chi-square test.

Where applicable for data visualization, data will be displayed graphically using pie or bar charts for categorical data and box-and-whisker plots, histograms, and column charts for continuous data. The independent sample “t” test will be utilized for group comparisons for continuously distributed data, and repeated measures ANOVA (Analysis of Variance) will be employed to evaluate the results across time and among the groups.

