Tang and colleagues have argued against starting early mobilization in the first few days, given the increased risk of the inflammatory response, which may exaggerate patients’ pain [5]. According to them and other authors, adhesions usually are not observed before the 10th day, and waiting for at least five days is recommended until the inflammatory phase is over [5–9]. However, the repaired tendons lose tensile strength significantly by two weeks and the excursion [5–7]. Therefore, it is recommended that mobilization be started from the fifth postoperative day onwards [5–9]. Mobilization decreases inflammation and helps reduce the work of flexion and friction [5–7]. As surgical methods and repair strength have increased, place and hold activities, synergistic wrist gliding exercises, and active gliding exercises have all been included in rehabilitation regimens [10]. These include immobilization regimens, place-and-hold exercises, and passive and active motion regimens [2, 3, 10]. Subsequently, many authors started studies on early active-motion protocols. As the evidence became clearer with improved functional results following early mobilization protocols, perhaps due to more efficient tendon gliding with minimized adhesions, the role of prolonged immobilization decreased. Later studies showed that tendons can heal without adhesion. In the only randomized study described for zone-5 injuries, Udayaraj et al. compared the Kleinert’s with a passive motion regime and observed the former to show better clinical improvement [11]. However, active flexion was not tested in these regimes, and the assessment duration was three months; hence, nerve injury and long-term assessment information were unavailable.

The main concern with active-motion programs is the risk of tendon rupture. However, the clarity on outcomes in the literature is lacking in view of variables like type and level of injury, technique of repair, and rehabilitation regimes [2, 8, 9, 12, 13]. Studies have also reported problems with passive mobilization protocols such as adhesions, joint contractures, and extensor lag [14]. For zone-5 flexor tendon injuries, no studies have compared the benefits of passive mobilization with early active motion therapy. In this regard, we propose conducting a randomized control trial (RCT) with the aim of comparing the functional results and complications of early active motion therapy versus passive mobilization for zone-5 flexor tendon injuries.

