### Study population

All patients aged 18–65 years qualifying for the inclusion criteria (vide infra) are considered for the trial. Comprehensive information encompassing enrollment, details of the surgery, plan of immobilization, associated benefits, risks, and complications, type of rehabilitation protocol, methods of evaluation during the follow-up, and assigned person of contact for queries and emergency events will be provided. The patient’s privacy will be protected, and those unwilling to continue the trial program will be allowed to exit the study unconditionally. Patients will be informed that they will be included in the active or passive flexion mobilization regime. Patients will be counseled to provide written informed consent.

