### Sample **size calculations**

At a 5% level of significance with 80% power and an effect size of 0.3, the minimum sample size (per group) required for a two-group repeated measures study design involving one primary quantitative outcome measured across four time points [six weeks, three months, six months, one year] (correlation among repeated measures is clinically presumed to be 0.3), was 44, i.e., 22 per group.

The sample size is computed using G*Power 3.1.9 and based on the formula mentioned below.

Formula.

$$n=\frac{2}{{{\delta ^2}}}\left[ {\mathop \sigma \nolimits_{b}^{2} +\frac{{{\sigma ^2}}}{k}\left[ {1+\left({k - 1} \right)\rho } \right]} \right]{\left({{z_{{\raise0.7ex\hbox{$\alpha $} \!\mathord{\left/ {\vphantom {\alpha 2}}\right.\kern-0pt}\!\lower0.7ex\hbox{$2$}}}}+{z_\beta }} \right)^2}$$

Where,

$$\mathop \sigma \nolimits_{b}^{2} $$: Between group variance

$${\sigma ^2}$$: Within group variance

$$\rho $$: Intra class correlation coefficient

$$\delta $$: Effect size

*K*: Number of repeated measures

$$\alpha $$: Significance level

$$1 - \beta $$: Power

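### The named repeated-measures ANOVA, in its classical form, uses only patients with all four visits, and the 44 patients leave no margin for any incomplete one

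*Protocol article*

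**What the plan says.** The Statistical analysis section of the protocol article says that "repeated measures ANOVA (Analysis of Variance) will be employed to evaluate the results across time and among the groups". It also lists an independent-samples t test for group comparisons. On software it says that "Programming or SPSS v23 will be utilized to analyze the data".

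The Sample size calculations section sets the design: "At a 5% level of significance with 80% power and an effect size of 0.3", a primary quantitative outcome "measured across four time points [six weeks, three months, six months, one year"], and "correlation among repeated measures is clinically presumed to be 0.3". The result "was 44, i.e., 22 per group" is described as a minimum. The Randomization and blinding section assigns exactly that number, 22 to each arm. No allowance for loss is stated.

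The Study population section says that "those unwilling to continue the trial program will be allowed to exit the study unconditionally". The Introduction says: "The main concern with active-motion programs is the risk of tendon rupture". It also gives the comparison of complications, alongside functional results, as an aim of the trial.

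**The concern.** Classical repeated-measures ANOVA, such as the SPSS GLM Repeated Measures procedure, needs a full set of measurements for each patient. A patient seen at three of four visits contributes nothing, so a modest share of missed visits can become a much larger share of lost patients. Here the method is paired with a sample size that meets its power target only if all 44 patients are complete for a year.

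Two things are at stake. The first is power for the between-group comparison, the test on which the trial appears to have been sized. The second is bias. If the patients who miss visits differ in outcome from those who attend, and differently by arm, an analysis of complete patients no longer compares the groups as randomised. Loss after tendon rupture is one example of how this could arise.

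**Working it through.** **Inputs from the protocol (Sample size calculations):** two-sided-equivalent F test at α = 0.05; effect size 0.3, read as Cohen's f; m = 4 visits; correlation ρ = 0.3; N = 44.

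**Inputs that are assumptions:** all loss rates. The protocol gives none.

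**Step 1. Reproduce the plan's figure.** For the between-group test in a repeated-measures design, the noncentrality is

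λ = f² · N · m / [1 + (m − 1)ρ], with 1 and N − 2 degrees of freedom.

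At N = 44: λ = 0.09 × 44 × 4 / 1.9 = 8.34, which gives power 0.805. This is the smallest even N that reaches 0.80, so the stated 44 is reproduced. The group-by-time interaction at the same inputs needs only 24 patients, so it is not the source of 44.

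**Step 2. Remove one patient.** At N = 43: λ = 0.09 × 43 × 4 / 1.9 = 8.15, power 0.796. At N = 42, power is 0.786.

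**Step 3. Loss concentrated in the same patients.** If a share d of patients is incomplete, N = 44(1 − d):

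| Patients incomplete (assumed) | Complete patients | Power |
|---|---|---|
| 5% | 41.8 | 0.784 |
| 10% | 39.6 | 0.761 |
| 20% | 35.2 | 0.708 |

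**Step 4. Loss scattered over visits.** If each visit is missed independently with probability p, the share of complete patients is (1 − p)⁴:

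| Missed per visit (assumed) | Complete patients | Power, complete patients only |
|---|---|---|
| 5% | 44 × 0.95⁴ = 35.8, about 36 | 0.72 |
| 10% | 44 × 0.90⁴ = 28.9, about 29 | 0.62 |

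**Step 5. The same scattered loss with all available visits.** Under a common correlation of 0.3, a patient with k visits contributes information k / [1 + 0.3(k − 1)]: 2.105, 1.875, 1.538 and 1.000 for k = 4, 3, 2 and 1. These are averaged over the binomial distribution of k, and λ = f² · 44 · (average information).

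- 5% missed: the average is 0.8145 × 2.105 + 0.1715 × 1.875 + 0.0135 × 1.538 + 0.0005 × 1 = 2.058. Then λ = 0.09 × 44 × 2.058 = 8.15, power about 0.80 (0.796).
- 10% missed: the average is 0.6561 × 2.105 + 0.2916 × 1.875 + 0.0486 × 1.538 + 0.0036 × 1 = 2.006. Then λ = 0.09 × 44 × 2.006 = 7.95, power about 0.79 (0.786).

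Under scattered loss, restricting the analysis to complete patients therefore costs about 8 points (0.80 against 0.72) or 17 points (0.79 against 0.62) relative to a model that uses every visit. These mixed-model figures are approximate: they use N − 2 denominator degrees of freedom and treat the covariance as known.

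**The case against.** The case against is substantial, and several parts of it stand.

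- **No deletion rule is written.** The protocol nowhere says that incomplete patients are excluded, and its wording leaves the software open. Deletion is how the classical procedure works, not a stated rule. Missing-data handling may sit in an analysis plan that is not shown, and its absence here is no fault. What remains open to criticism is the method that the protocol does name, together with a sample size that has no margin.
- **Withdrawal is permitted, not forecast.** The sentence on leaving the study is an ordinary ethical provision. The protocol also excludes patients unable to attend therapy and assigns staff to a year of follow-up. Loss may be small, and at 5% to 10% of patients incomplete the cost is only about 2 to 4 points.
- **The scattered pattern is the harsher one.** If the same few patients miss several visits, Step 3 applies rather than Step 4. The mixed model then also recovers less, and it recovers nothing from a patient who is never measured.
- **Not every comparison is affected alike.** A t test at a single visit uses everyone seen at that visit, and the interaction test keeps power of 0.92 at the same f with 30% incomplete. The Statistical analysis section does not expressly tie the ANOVA to the primary outcome, although the sample-size design points that way.

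A reader might go further and infer that patients with a rupture are the ones most likely to disappear from the analysis, so that active motion would look better than it is. The protocol does not support that. It gives no rupture rate, no rule that removes such patients from follow-up or analysis, and no evidence of more ruptures in either arm of this trial. A patient with a rupture can still have total active movement (TAM) measured. The protocol also says that treatment of complications and revision surgery will be paid for, which may help to keep such patients in contact.

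**Conclusion.** The point holds in a limited form. The protocol names a method that classically needs all four visits and randomises exactly the number required when every patient is complete. Any incomplete patient takes the between-group test just below the stated 80%. How far below depends entirely on loss that the protocol does not quantify: about 0.78 to 0.71 if 5% to 20% of patients are incomplete, and 0.72 or 0.62 if 5% or 10% of visits are missed independently.

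These figures rest on reading 0.3 as Cohen's f for the between-group test, a reading supported by its reproducing 44, and on analysing complete patients only. Bias from loss related to outcome, for example after rupture, is a possibility to guard against and not something that the document shows. The change is worth making because a better method is available at almost no cost.

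**What to change.** Replace the repeated-measures ANOVA for the primary outcome with a linear mixed model for TAM:

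- fixed effects for arm, visit and arm-by-visit;
- one pre-specified within-patient covariance structure, fitted by REML;
- every available TAM measurement from all randomised patients, in their allocated arm;
- the arm effect averaged over the four visits as the primary contrast.

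Add a sensitivity analysis that counts rupture or re-operation as a poor outcome. Report rupture per arm with an exact confidence interval, since comparing complications is a stated aim. With 22 patients in an arm, even no ruptures leaves an exact 95% upper limit of 1 − 0.025^(1/22) = 15%.

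The cost is a change of wording, and the model can be fitted in SPSS. The downside is that it relies on data missing at random and does not by itself correct loss that depends on unobserved outcomes; the sensitivity analysis is there for that reason. If the sponsor also wants an explicit allowance for loss, 44/(1 − d), rounded up to an even number, gives 48, 50 or 56 patients for an assumed d of 5%, 10% or 20%. That would require further recruitment, whereas the change of model does not.

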### Data management

A distinct number will be given to each patient, and this number will be used to record all clinical information. Perioperative assessment and examination will be the responsibility of the consultant hand surgeon and the clinical resident. The research associate will oversee the postoperative evaluation, and the associate hand surgeon will be blinded. The research associate and clinical resident will conduct routine follow-ups for a year after surgery. Using the designated computer, the Principal Investigator will oversee data entry and storage. After data gathering, an electronic database will be created and backed up. After this study, all raw data will be kept in a medical recording room for at least three years.

### **Data** monitoring **and auditing**

The principal investigator in charge of the research study will ensure and confirm that each participant has signed an informed consent form before beginning the study. He/she will also ensure that the research adheres to the study protocol, upholds all pertinent laws, and collects accurate and comprehensive data and observations. The data monitoring committee, composed of three experts in hand therapy, occupational therapy, and statistics, will perform audits via phone calls or routine interviews. They also maintain the power to examine patients at random on any occasion. The audit procedure will be completed without the involvement of the investigators’.

### Strategies **to improve adherence to protocol**

To conduct the recruitment process, we will obtain informed consent and follow-up and standardize the evaluation scales to assess outcomes; all study members will undergo an informative, professional training program.

### **Ethics** and **dissemination**

The Institute Ethics Committee endorsed the trial (approval No. IEC – 383/2022). The study design and informed consent documents addressed the minimal potential risks of this RCT. Each candidate fulfilling the inclusion criteria will provide written informed consent before the enrolment. The trial is registered at the Clinical Trial Registry of India (CTRI)(registration number: CTRI/2023/03/050721). The data from this trial and the CTRI registration and IEC approval form will be submitted together. The principal investigator will pay for any secondary revision procedure. The results of this trial will be shared and published in academic forums and peer-reviewed research journals. Relevant authorities, including trial registries and the institute ethics committee, will be informed of protocol modifications (e.g., interventions, sample size changes, outcomes, and analyses).

### Patient **and public involvement**

The planning, execution rep, sorting, or distribution of the study will not involve patients or members of the public.

## Discussion

The proposed novel study of a double-blind, randomized trial conducted at a single center, comparing the functional results of early active motion therapy with passive mobilization in zone-5 flexor tendon injuries, is unique and has not been described earlier. It will answer the role and possible benefits of a more aggressive early active mobilization program. Additionally, the study will give information on patient-reported outcomes and address the incidence of complications.

How successfully a flexor tendon heals depends on several factors, including the type of injury, any concurrent nerve damage, the surgeon’s experience, treatment methods, and postoperative care [2, 8, 9, 20]. Several different postoperative mobilization techniques exist, from rigid immobilization to early, protected finger movement. However, the description of the rehabilitation program after flexor tendon surgery in zone-5 is not well documented in the literature [21]. The only regime followed for injury in these regimes was a form of early protected passive range movements. The majority of the studies reported acceptable function with early mobilization, with a higher complication rate being observed in more severe tendon and nerve injuries [2, 10, 22–24].

In one of the earliest reports on a comparison study between active and passive mobilization regimes for zone-5 flexor tendon injuries, Panchal et al. reported results observed in two each cadaver and patients [4]. The mean excursion of the FPL, FDP, and FDS will be calculated at three time periods of 10 days, three, and six weeks. The authors found an ‘increased’ excursion in patients who followed the active flexion mobilization program [4]. Although early active mobilization has been advocated since then, true active flexion regimes have been described in very few studies, and no comparisons have been made between different methods [3]. Yii et al. did a prospective study in zone-5 flexor tendon injuries and introduced an active extension and active flexion regime [25]. A series of 52 patients with an average of 10 months follow-up showed independent FDS activity in 66%, with 90% achieving good to excellent results concerning range of motion [25]. However, this series also included non-Spaghetti injuries, and ‘Spaghetti injury’ was attributed as a risk factor for adverse results. Udayraj et al. have compared Kleinert’s protocol (which involves the active extension of the digit program) with a passive range of movement regime in a randomized study involving 30 patients [11]. They demonstrated a better clinical improvement in Kleinert’s protocol when compared to the passive mobilization group [11]. However, only the total active movement and grip strength were measured, and the study period was a limited duration of 12 weeks. The current proposed study addresses all these issues as we plan to evaluate multiple parameters over a one-year period.

In the last two decades, significant advances have helped in the understanding of flexor tendon healing, resulting in better techniques in exposure, repair, and rehabilitation [2, 26, 27]. Much emphasis has been put on early active flexion of the injured digit as the new repair techniques have permitted a greater load on the repair site [5]. However, most of this research work has been done for the region of zone 2. The current authors believe this can also be applied to Zone 5. However, it must be compared with the existing passive mobilization protocol to confirm its benefits.

In a systematic review of outcome measures used for zone-5 injuries, Cardozo et al. observed a lack of consistency in the outcome measures used for assessment [10]. They observed eight measures used in different studies, with the TAM being the most common [10]. We have used the TAM with Tang’s criteria to document quality improvement. The sensory-motor recovery has also been added, as suggested by Cardozo et al. We have also introduced the patient-reported outcome measure of MCHQ to make it a more comprehensive evaluation.

The limitations of this research are primarily associated with it being conducted within a singular institutional framework. Nevertheless, it will ensure uniformity in the management of the patients. To summarize, the purpose of this research is to ascertain the minimal duration of immobilization required to ensure sufficient healing of a flexor tendon repair in zone 5 under the condition that a standardized rehabilitation protocol is implemented.

## Data Availability

No datasets were generated or analysed during the current study.
